| Sample size (14) | The sample size is estimated based on the following assumptions: among women at three months postpartum, KDHS data report 27% of use of any method (modern or traditional) in Kenya while the CPR in the general population is 53% (KNBS, 2015) . These figures allow the assumption of a desired 26% difference between control and the intervention groups (26% increase in adopting a modern contraceptive by three months postpartum). Therefore the sample size was calculated pairwise for two separate RCT for community arm and the control and the facility arm and the control (Fleiss et al., 2004; Freidlin et al., 2008; Kane, 2018; Rosner, 2015). Rosner, 2015 proposed the sample size determination formula for difference in proportions with consideration of type I and II errors and power (Rosner, 2015; Suresh & Chandrashekara, 2012), N1={z_(1-α/2)*√(p ̅*q ̅*(1+1/k) )+z_1-β*√(p1*q1+(p2*q2)/k)}^2/Δ^2  Where q1=1-p1, q2=1-p2, p ̅=(p1+kp2)/(1+K) , p1, p2 = proportion (incidence) of groups #1 (27%) and #2 (53%) , Δ = |p2-p1| = absolute difference between two proportions (0.26), n1 = sample size for group #1, n2 = sample size for group #2, α = probability of type I error (is set at 0.05), β = probability of type II error (is set at 0.1 i.e. 90% power), z = critical Z value for a given α or β(1.96) and K = ratio of sample size for group #2 to group #1(1). Thus for practical equal sample distribution, the actual sample size shall be 246. Each facility shall have 41 clients |

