| Recruitment (15) | Each health centre and community unit will have a trained research assistant. The assistant is to ensure adherence to the study manual and standard operating procedures for data management. The primary outcomes will largely be assessed based on the CRFs, appointment card and questionnaire. Actual uptake of modern contraceptive method will be established three months postpartum between the 12th to 14th weeks after birth. The CRFs will be filled on recruitment by the trained ANC service provider. The appointment card will be filled by the health worker after the client has accepted to set postnatal follow up date for PPFP. The questionnaire will be filled at 14 weeks postpartum during the scheduled MCH visit by a trained enumerator.  The client exit interview guide and site visit appraisal form will be used to assess the process indicators. Client exit interviews will be done by trained enumerator on the earliest opportunity after the intervention has been administered to reduce recall bias by the client. Site appraisal form will be filled on site visits by the research team and on the part of enumerator will be filled each day to include workload for ANC, number of staff available to offer ANC services, availability of FP counselling bag and flipchart. Lose to follow-up will be called to find the status of the client |
| **Methods: Assignment of interventions (for controlled trials)** | |
| Allocation: |  |
| Sequence generation (16a) | Each client meeting the criteria will be randomly assigned to the study i.e. to the intervention and to the control arms using simple random sampling by picking folded paper labelled “yes” or “no”. There will be no blinding as the intervention facilities and controls are known and will be separate to reduce contamination. |
| Allocation concealment mechanism (16b) | There will be no allocation concealment as the intervention and control facilities are known and separate to reduce contamination. |
| Implementation (16c) | The allocation to intervention and control is at the facility level. The participants will be enrolled by the study nurse for both the community and facility arms. Participants will be assigned to participate by picking a ballot paper labelled “yes” or “no” enclosed in resembling envelopes |
| Blinding (masking) (17a,b) | None of the implementers and participants will be blinded thud there equally no plan for controlled unblinding. |

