| Statistical methods (20a,b,c) | Quantitative data entry will be done in IBM’s SPSS version 26. The sub-Country research teams will be responsible for verifying the data and a second verification will be done by the researcher to monitor data quality. Questions about data inconsistencies or missing values will be sent to sites and will be resolved on an ongoing basis. The participant will form the unit of analysis and intra-cluster correlation coefficient will be accounted for. All analysis will be by intention to treat Descriptive statistics will be performed by computing means, standard deviations, and minimum and maximum values for continuous variables, and frequencies and percentages for categorical variables. As part of quality control and descriptive analysis of the data, the distribution of variables to detect outliers will be examined. Descriptive statistics will be tabulated for individual clusters and aggregated across clusters.  On evaluating the effect of socio-cultural beliefs on Postpartum Family Planning uptake among postpartum mothers in Kisumu County, descriptive statistics on of prevalent sociocultural beliefs about PPFP will be summarized into frequencies and percentages. Bivariate analysis of effects of sociocultural beliefs on PPFP uptake will be done and presented on two-by-two (2x2) tables with Chi-square being the inferential statistics where P-value will determine the significance of homogeneity of proportions and odds ratio (OR) and 95% confidence interval (95% CI) will demonstrate the strength of the relationship. Binary logistic regression analysis will be done to adjust for confounders of sociocultural beliefs as determinants of PPFP uptake  Perceived individual control of Postpartum Family Planning choice among postpartum mothers in Kisumu County will be analysed using descriptive statistics aggregated based on sociodemographic aspects and presented in tables with means, median, range and standard deviation. This will further be analysed by student t-test to ascertain the significance in differences in means for the determinants of perceived control of family planning choice Significant determinants will be fitted in multilinear regression analysis to adjust for confounders  Fertility intentions for postpartum mothers will be disaggregated based on sociodemographic aspects and other individual characteristics. Intention to use PPFP will be simplified in proportions of the categorical yes or no to appointment for PPFP. Bivariate analysis of determinants of fertility intentions will be done and presented in two-by-two (2x2) tables with Chi-square being the inferential statistics. Binary logistic regression analysis will be done to adjust for confounders of determinants of fertility intentions.  Likewise, level of intention will be measure by Likert scale and analysed by t-test statistics after normality testing and adjusted for in linear regression analysis.  Postpartum Family Planning uptake between control and intervention groups of will be compared by use of simple clinical superiority in the proportions.  Bivariate analysis with chi-square statistics will be used to analyse the determinants of Postpartum Family Planning uptake between control and intervention groups and thus will form the selection criteria for inclusion in final regression model. Binary logistic regression analysis will be applied to adjust for confounders |

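### The sample size has no allowance for clustering although each site carries one arm only, so the stated 90% power is unsupported and fails for any intra-cluster correlation above about 0.003

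*Protocol*

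**What the plan says.** Protocol, Sample size (14), uses a formula for the difference between two independent proportions, applied separately to facility versus control and to community versus control. Its inputs are "proportion (incidence) of groups #1 (27%) and #2 (53"%), "absolute difference between two proportions (0.26"), "α = probability of type I error (is set at 0.05") and "β = probability of type II error (is set at 0.1 i.e. 90% power"), with equal groups. It ends: "Thus for practical equal sample distribution, the actual sample size shall be 246. Each facility shall have 41 clients". The section contains no ICC, design effect or number-of-clusters term.

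Other sections describe a clustered design:

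- Trial design (8) calls the study a cluster RCT with three arms.
- Study setting (9) names two intervention health centres, two intervention community units, and two control health centres with their linked units. Each belongs to one arm.
- Implementation (16c) states: "The allocation to intervention and control is at the facility level".
- Statistical methods (20a,b,c) states: "The participant will form the unit of analysis and intra-cluster correlation coefficient will be accounted for".

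Two places read differently. Trial design (8) also says that randomisation to arms is at individual level within the selected sites. Sequence generation (16a) has each client assigned to intervention or control by drawing a folded paper.

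**The concern.** When whole sites carry a single arm, women at the same site tend to resemble each other in uptake, and that shared variation goes directly into the difference between arms. A formula for independent women leaves it out and so overstates the precision of the comparison. The protocol recognises clustering in its design label and in its analysis, but not in the calculation that justifies 246.

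The power figure governs how a null result will be read. A reader told 90% would think a 26-point difference very unlikely to have been missed. If the true power is nearer 50%, it would be missed about half the time.

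**Working it through.** **Inputs from the protocol.** p1 = 0.27, p2 = 0.53, difference 0.26, two-sided α = 0.05 (the formula uses z at 1−α/2), power 0.90, k = 1 (Sample size 14). Women per site m = 41. Sites: 246/41 = 6, so two per arm and 2 × 41 = 82 women per arm. **Not in the protocol:** an ICC, so a range from 0 to 0.10 is assumed.

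**Step 1: the plan's own figure.** With p̄ = 0.40:

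- 1.96 × √(2 × 0.40 × 0.60) = 1.3579
- 1.2816 × √(0.27 × 0.73 + 0.53 × 0.47) = 1.2816 × 0.6680 = 0.8561
- n = (1.3579 + 0.8561)² / 0.26² = 4.902 / 0.0676 = 72.5, so 73 per arm and 219 over three arms

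The protocol states 82 and 246 and shows no step from 73 to 82. Two unstated routes come close. A Fleiss-type continuity correction gives 80 to 81, which an even split over two sites of 41 takes to 82. A 10% loss allowance gives 73/0.9 = 81.1, so 82. Both assume independent women.

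**Step 2: room for clustering.** The design effect is DE = 1 + (41 − 1) × ICC. The largest DE that 82 can absorb at 90% power is 82/72.5 = 1.13, so the break-even ICC is (1.131 − 1)/40 = 0.0033. If the extra women were meant to cover loss to follow-up, even that room is gone.

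**Step 3: power with 82 per arm.** Effective n = 82/DE, and power = Φ[(0.26 × √n_eff − 1.3579)/0.6680]. The last column is the difference above 27% detectable with 90% power, found by solving the same formula for p2 at that effective n.

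| ICC (assumed) | DE | Effective n per arm | Power for 26 points | Detectable difference |
|---|---|---|---|---|
| 0 | 1.0 | 82.0 | 93% | 24 points |
| 0.01 | 1.4 | 58.6 | 83% | 29 points |
| 0.02 | 1.8 | 45.6 | 72% | 33 points |
| 0.05 | 3.0 | 27.3 | 50% | 42 points |
| 0.10 | 5.0 | 16.4 | 32% | 53 points |

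Power falls below 80% once the ICC exceeds about 0.013.

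**Step 4: the limit from two sites per arm.** As women per site increase without bound, effective n per arm approaches 2/ICC. At ICC 0.03 that is 66.7 (power at most 87%), and at ICC 0.05 it is 40 (at most 67%). Above those values more women at the same sites cannot restore 90%.

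**The case against.** **Randomisation may be individual.** Trial design (8) and Sequence generation (16a) can be read that way, and if both arms were drawn within each site this design effect would not apply. But Study setting (9) gives each named site one arm. Allocation concealment (16b) says intervention and control facilities are known and separate, and 16c describes the yes/no ballot as assignment to participate. A draw within a site that carries one arm cannot remove site-level correlation from the arm contrast. What stands is that the sections conflict and need reconciling.

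**The margin from 73 to 82 may cover clustering.** Nothing says so, and it would cover an ICC of only about 0.003.

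**The power may not be that low.** This stands in part. No ICC is given, so a reader might infer that the trial could not detect its target effect. The documents do not support that: at ICC 0.01 the normal approximation still gives 83%.

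**A test on site means would be far worse.** With two sites against two, a cluster-level t-test on 2 degrees of freedom gives about 48% power even at ICC 0. A reader might take that as the trial's real power. Statistical methods (20) does not specify such a test: it makes the participant the unit of analysis with the ICC accounted for. The figure is a caveat about so few sites.

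**Inflating 73 by the design effect might seem to give the right number of women.** At ICC 0.02 that is 73 × 1.8 = 131.4, or about 131 to 132 per arm. It assumes 41 per site and so needs 131.4/41 = 3.2 sites per arm, but the trial has two. With two sites, about 66 per site gives DE = 1 + 65 × 0.02 = 2.3 and about 82% power; reaching 90% would take about 258 per arm.

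**Conclusion.** The concern holds in conditional form. The stated power ("is set at 0.1 i.e. 90% power") rests on independence between women at the same site, which neither the single-arm sites nor the promised analysis supports. It fails for any ICC above about 0.003. Over an assumed ICC range of 0.01 to 0.05, power for the 26-point difference is about 83% down to 50%.

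These figures assume two sites of 41 per arm, complete follow-up, the normal approximation, and the reading that each site carries one arm. That reading is the better supported one, though the protocol is not consistent about it. The exact loss of power cannot be stated without an ICC. The defect is a missing design assumption: the printed formula itself is a standard one.

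**What to change.** Keep 246 women. In Sample size (14):

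- Replace the unqualified 90% with power and detectable difference under DE = 1 + 40 × ICC, for a stated ICC range such as 0.01 to 0.05.
- Say that the figure without clustering (about 93% by the printed formula) holds only if women are independent.
- State the limit imposed by two sites per arm.

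Reconcile the unit of randomisation across Trial design (8), Sequence generation (16a) and Implementation (16c), because the power statement depends on it.

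The cost is a protocol wording change and a less favourable stated power. No additional participants are needed.

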| Protocol amendments (25) | Plans for communicating important protocol modifications (eg, changes to eligibility criteria, outcomes, analyses) to relevant parties (eg, investigators, REC/IRBs, trial participants, trial registries, journals, regulators)  Protocol amendments will be communicated by the PI to the Pan-African Clinical Trials Registry (PACTR), British Medical Journal (BMJ) (Journal for Trials), MMUST Institutional Ethics Review Committee (IERC) and NACOSTI |
| Consent or assent (26a,b) | The trials nurse at each site will obtain the consent from the trial participants |
| There will be no need for additional consent provisions to use individual participant’s data and biological specimens as the study will not publish individual participant data but anonymous group data and there are no biological specimen being collected. |
| Confidentiality (27) | Personal information about potential and enrolled participants will be collected using kobo tool box and submitted by the study nurse or CHW to the study server. Individual participants will be allocated randomly generated enrolment numbers to maintain anonymity all through the trial period. Access to data will be password encrypted. |
| Declaration of interests (28) | GG is the Chief officer of Health in Kisumu County but is not directly involved in care provision of the essential services to the study participant. The county government of Kisumu nurses employed in the facilities and the Community Health Assistants (CHA) will be the implementers of the intervention. All other core team members declare that they have no conflict of interest. |
| Access to data (29) | Access to trial dataset will be controlled. Request to be done by email to the principal investigator The decision is by the Research team lead by the Principal investigator. Criteria for reviewing the request: Qualification of the person requesting, description of the purpose of the request, willingness to engage the Principal investigator in the development of analysis plan, and monographs or manuscripts. |
| Ancillary and post-trial care (30) | No harm is anticipated in this trial thus no defined ancillary and post trail compensation. |

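### The yes/no paper draw at enrolment has no declared concealment and no described record, and the protocol contradicts itself on whether it decides arm or participation

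*Protocol*

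**What the plan says.** Four protocol items describe how a woman enters the trial.

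- **Sequence generation (16a):** eligible women are divided between intervention and control "using simple random sampling by picking folded paper labelled" with one of two answers, yes or no.
- **Allocation concealment mechanism (16b):** the item rules this out in one sentence: "There will be no allocation concealment as the intervention and control facilities are known and separate to reduce contamination". It offers no other reason.
- **Implementation (16c):** here the arm belongs to the site, since "The allocation to intervention and control is at the facility level". Enrolment is the task of a single role: "The participants will be enrolled by the study nurse for both the community and facility arms". A ballot marked yes or no then settles whether the woman takes part, and the ballots are "enclosed in resembling envelopes".
- **Blinding (17a,b):** neither implementers nor participants are blinded.

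Trial design (8) calls the study a cluster randomised trial, yet places randomisation to arms at the individual level within the selected sites. Study setting (9) names the intervention facilities, the intervention community units and the control sites, so each site has one arm. Participant timeline (13) has recruitment and intervention taking place together.

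**The concern.** Concealment and blinding are different safeguards. Blinding hides the treatment after entry. Concealment hides the next assignment until the woman's eligibility and consent are settled. Item 16b uses the fact that sites are known to dispense with concealment. That fact explains why blinding is impossible, but it gives no reason to leave the draw itself unprotected or unrecorded.

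The main outcome is uptake of a contraceptive method, a personal choice likely to depend on how keen the woman already was. If entry to an intervention site leans towards keener women, the arms differ before any counselling. Intention to treat does not correct this, because it governs women after entry. The planned logistic regression can adjust only for what is measured. Under Outcomes (12), intention, attitude and perceived control are measured after the intervention in the intervention arms; for attitude and perceived control, the controls are measured at recruitment. In the intervention arms these measures are not an untouched baseline.

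The contradiction over what the draw decides matters as much, because both the route of bias and the remedy depend on it.

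**Working it through.** **1. What the draw decides**

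| Reading | Where | What the draw sets | What could go wrong |
|---|---|---|---|
| Individual | Trial design (8), 16a | Arm | A draw could be steered or repeated, altering a woman's arm |
| Facility | 16c, the reasons given in 16a and 16b, and the named sites in Study setting (9) | Participation at a site of fixed arm | Arm cannot be altered, but someone who knows the arm can influence who enters (recruitment bias) |

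Both readings cannot be true. If each site has one arm, an individual draw between arms has nothing to decide.

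**2. Which safeguards are stated**

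Stated: folded papers (16a) and envelopes of similar appearance (16c). Not stated anywhere in the protocol: a sequence generated beforehand, an independent holder of the papers, sealing, opacity, numbering, a log of draws that includes each no, or a rule against drawing again. Item 16b then disclaims concealment outright.

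**3. Illustration of size**

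Inputs from Sample size (14): 27% uptake in controls, 53% in the intervention group, two-sided alpha 0.05, total 246, 41 per site. Arm size is 246 / 3 = 82, which is two sites of 41.

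For the record, the printed formula gives 72.5, so 73 per group and 219 for three groups. With a continuity correction it gives 81 and 243. With an assumed 10% dropout, which the protocol does not state, 73 / 0.90 rounds up to 82, hence 246. The point here does not depend on which route was used.

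Assumption A: a share *s* of an intervention arm consists of women admitted by a steered or repeated draw. Assumption B: those women would have 53% uptake without any counselling. The protocol gives 53% as the general-population rate and as its target for the intervention group, not as the uptake of keen women under routine care.

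- Spurious difference: d = s × (0.53 − 0.27) = 0.26 s
- Standard error with no true effect: √(2 × 0.27 × 0.73 / 82) = 0.0693
- Rejection probability: 1 − Φ(1.96 − d/0.0693) + Φ(−1.96 − d/0.0693)

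| Share steered | d (points) | d / SE | Rejection probability |
|---|---|---|---|
| 10% | 2.6 | 0.375 | 6.6% |
| 20% | 5.2 | 0.750 | 11.7% |
| 30% | 7.8 | 1.125 | 20.3% |

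Using the variance of the biased arm instead gives 6.6%, 11.2% and 19.0%. If one instead assumes a shift of 5, 10 or 15 points directly, the same test rejects in about 11%, 28% or 52% of trials. The spread shows how far the answer depends on assumptions. None of these figures allows for clustering.

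**The case against.** A reader might infer that the draw is fully open and that the nurse can choose who enters each arm. The documents do not support that. The papers are folded and the ballots are in similar-looking envelopes, so the result is at least partly hidden until picked. On the wording of 16c it is the participant who picks. If allocation is by facility, nobody can move a woman between arms. The protocol nowhere permits a second draw after a no; that possibility is inferred from silence.

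There is also some oversight. The data management team tracks those who accepted against those sampled (Data monitoring, 21a,b), and the trial is audited monthly (Auditing, 23). The enroller is not always the person who counsels: community health assistants are trained for the community arm, while the study nurse enrols. The planned regression could reduce an imbalance in measured factors.

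All of this stands and narrows the point. It does not remove it. Similar envelopes do not stop another being opened, and 16b still declares no concealment. An acceptance rate and a monthly audit are not a record of draws and cannot show whether a particular draw was respected. The nurse who enrols knows the site's arm whoever delivers the counselling. Regression cannot adjust for prior intention unless it is recorded before counselling.

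**Conclusion.** The point holds in this form: the protocol states an unconcealed paper draw, describes no means of checking it afterwards, and is inconsistent on whether the draw sets arm or participation. Under the individual reading, allocation can be steered or repeated. Under the facility reading, the exposure is the narrower one of recruitment bias at sites of known arm, which intention to treat does not correct and adjustment can only partly reduce.

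This is a weakness that the stated rules leave open, not a prediction that staff will misuse the draw. A reader might take 6.6% to 20.3% as the trial's actual false-positive rate; the documents do not support that, since both the share steered and the 53% uptake of those women are assumed. The protocol should be amended, and the case for doing so rests on the stated procedure, not on these figures.

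**What to change.** **First, reconcile Trial design (8) and 16a with 16c**, so that one level of allocation is stated throughout.

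**If allocation is individual:** replace the paper draw with a list generated before enrolment. Release one entry at a time, only after the woman's eligibility and consent form is saved, and log every entry. Reword 16b to say that the next entry is hidden from the enrolling nurse. The description of separate, single-arm sites would also have to change, since it cannot coexist with this reading.

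**If allocation is by facility:** drop the draw. Enrol consecutive eligible, consenting women until the site has 41. Keep a log of all women screened, approached and declined, with reasons. Record family-planning intention before any counselling in every arm and adjust for it. State plainly that the recruiter still knows the arm, so consecutive enrolment reduces recruitment bias but leaves some of it.

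**Cost:** a protocol amendment and one form step at enrolment, plus the log and a short baseline question under the facility option. Enrolment data already go through Kobo, and Confidentiality (27) says "Individual participants will be allocated randomly generated enrolment numbers to maintain anonymity". The protocol does not say that Kobo generates those numbers or can release allocations, so that step needs to be confirmed. A device must be at hand when women are enrolled.

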| Eligibility criteria (10) | This study will be among pregnant mothers in their third trimester, irrespective of age, attending ANC clinic in the intervention facilities or are within the respective CUs followed up to 3 months postpartum. The study will be conducted in 4 primary health centres and 2 community units in Kisumu East sub county. The Health centres eligibility depended on if: they offer the continuum of ANC, delivery, and PNC; they provide a selection of at least three modern contraceptive methods that are rated 2 or 1 on the Medical Eligibility Criteria (MEC) for postpartum contraceptives and there were no stock-outs of contraceptives during the preceding six months |
| Interventions (11a/b/c/d) | The intervention will be; provision of antenatal information on PPFP using a standardized PPFP counselling tool and postpartum appointment setting. The control group will be under the routine standard antenatal care. There will be antenatal PPFP information provision training for the service providers at the facility and Community Health Assistants (CHA) for the community arm to standardize the intervention. The intervention will be administered in the second and third trimester of pregnancy. The study nurse or CHA will use a standardised tool of Medical Eligibility Criteria |
| Client can be discontinued if they lose their only sexual partner, the only sexual partner undergoes vasectomy in the course of pregnancy, develop postpartum psychosis, are hospitalized for more than 14 weeks postpartum. |
| Client exit interviews returns to data base and the dashboard will be reviewed by the data management team to give feedback to the study steering committee for appropriate corrective actions to improve adherence to intervention protocols |
| The is no concomitant care or intervention that is recommended or prohibited during the trial |

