| **Methods: Data collection, management, and analysis** | |
| Data collection methods (18a,b) | Each health centre and community unit will have a trained research assistant. The assistant is to ensure adherence to the study manual and standard operating procedures for data management. The primary outcomes are; PPFP knowledge, the intent for use of PPFP (behavioural contracting) and the actual uptake of modern contraceptive methods at three months postpartum will largely be assessed based on the CRFs, appointment card and questionnaire. Actual uptake of modern contraceptive method will be established three months postpartum between the 12th to 14th weeks after birth. The CRFs will be filled on recruitment by the trained ANC service provider. The appointment card will be filled by the health worker after the client has accepted to set postnatal follow up date for PPFP. The questionnaire will be filled at 14 weeks postpartum during the scheduled MCH visit by a trained enumerator.  A process evaluation will be undertaken with the objectives of understanding the barriers and enablers related to the delivery of PPFP. This will be evaluated based on client exit interviews and site appraisal forms. The client exit interview guide and site visit appraisal form will be used to assess the process quality indicators which will include: waiting time, time/trimester of start of FP counselling, time after FP counselling, group/ individual session, availability of teaching aid on the table during counselling, gauging FP information level, application of GATHER (Greet, Ask, Tell, Help, Explain and Return/Refer) Model and BRAIDED (Benefits, Risks, Alternatives, Inquiries, Decision, Explanation, Documentation) Model. Satisfaction with information given, responses to questions, respectful care, confidentiality and privacy. Client exit interviews will be done by trained enumerator immediately after the intervention has been administered to reduce recall bias by the client. Site appraisal form will be filled on site visits by the research team and on the part of enumerator will be filled each day to include workload for ANC, number of staff available to offer ANC services, availability of FP counselling bag and flipchart. |

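### Knowledge and intention appear to be recorded by unblinded care staff, who in the facility arm also deliver the counselling, and card-based intention is not comparable with controls

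*Protocol*

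**What the plan says.** **Who delivers.** Interventions (11a/b/c/d) defines the intervention as structured antenatal counselling plus the setting of a postpartum appointment; controls get routine antenatal care. On training it says: "There will be antenatal PPFP information provision training for the service providers at the facility and Community Health Assistants (CHA) for the community arm". Declaration of interests (28) confirms that county "nurses employed in the facilities and the Community Health Assistants (CHA) will be the implementers of the intervention".

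**Which outcomes, from which tools.** Data collection methods (18a,b) and Data management (19) state: "The primary outcomes are; PPFP knowledge, the intent for use of PPFP (behavioural contracting") and actual uptake, and that these "will largely be assessed based on the CRFs, appointment card and questionnaire". The registration table and Outcomes (12) instead make uptake the main outcome, with intention and knowledge secondary.

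**Who fills the tools.** For the CRF: "The CRFs will be filled on recruitment by the trained ANC service provider". For the card: "The appointment card will be filled by the health worker after the client has accepted to set postnatal follow up date for PPFP". The questionnaire is completed at 14 weeks by an enumerator.

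**How intention is analysed.** Statistical methods (20a,b,c): "Intention to use PPFP will be simplified in proportions of the categorical yes or no to appointment for PPFP".

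**What else happens at that moment.** Participant timeline (13) makes recruitment and intervention simultaneous. "Client exit interviews will be done by trained enumerator immediately after the intervention has been administered to reduce recall bias by the client", but the exit interview is assigned to process indicators. Blinding (17a,b) says that neither implementers nor participants are blinded.

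**The concern.** An outcome measured straight after counselling is open to influence from whoever records it. If that person has just done the counselling and knows the arm, a doubtful answer may be prompted or written down favourably. Control staff have delivered no study counselling, so any such error need not be equal between arms, and its likely direction is toward the intervention. Randomisation and intention-to-treat analysis do not remove it.

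Intention has a second problem. The card records acceptance of something that only the intervention offers. A between-arm difference in acceptance then partly shows that one group was offered an appointment and the other was not.

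At stake are the between-arm results for knowledge and intention, which two sections of the protocol call primary. If attitude and perceived control, measured at the same time, are taken on the same forms, they are exposed too.

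**Working it through.** **Step 1. Which tool carries which outcome.** The protocol has no outcome-by-tool table, so this goes by elimination among the three named tools.

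| Tool | Filled by | When | Could it carry knowledge right after counselling? |
|---|---|---|---|
| CRF | trained ANC provider | recruitment, i.e. with the intervention | yes |
| Appointment card | health worker | once the client accepts | unlikely: Data management (19) gives it client details, a proposed start date and an information summary |
| Questionnaire | enumerator | 14 weeks postpartum | no, too late for the timing in Outcomes (12) |

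The CRF is left for knowledge. The order in which outcomes and tools are listed agrees, but the protocol never says so outright. For intention the link is closer: the analysed variable is yes/no to the appointment, and the card records acceptance.

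**Step 2. Whether recorder and counsellor are the same.**
- Facility arm: trained facility providers counsel, and the trained ANC provider fills the CRF. They are the same group of staff.
- Community arm: the CHA counsels, while the CRF sentence names the ANC provider and Implementation (16c) has the study nurse enrol for both arms. Confidentiality (27) has the study nurse or community health worker submit participant information. The overlap is possible but not established.
- Control arm: the CRF sentence is not limited by arm, so a provider presumably fills it here too, without having delivered the intervention.

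**Step 3. Whether intention is comparable.** Outcomes (12) gives a control time point (recruitment) for knowledge, perceived control and attitude, but none for intention. Appointment setting belongs to the intervention. The comparison is therefore unbalanced whoever fills the card.

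**Step 4. Size, as illustration only.** The protocol has no figure for recording bias, so there is none to reproduce. The only planned number used is the arm size: 246 / 3 = 82, or two sites of 41. (For 27% against 53%, two-sided 5% and 90% power, the printed formula gives 73 per arm, and 81 with a continuity correction. Nothing below depends on this.)

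Assume no true effect, independent women, a common proportion p and a spurious shift d in one intervention arm.

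SE = √(2p(1−p)/82); rejection rate = Φ(d/SE − 1.96) + Φ(−d/SE − 1.96)

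| p | SE | d = 5 points | d = 10 points |
|---|---|---|---|
| 0.27 | √(2×0.27×0.73/82) = 0.069 | 11.1% | 30.3% |
| 0.40 | √(2×0.40×0.60/82) = 0.0765 | 10.0% | 25.7% |
| 0.50 | √(2×0.50×0.50/82) = 0.078 | 9.8% | 24.9% |

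The nominal rate is 5%. The 27% is the protocol's figure for contraceptive use at three months, borrowed as a low base rate; it is not a figure for knowledge or intention.

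A milder model lets a share f of true negatives be recorded as positive, so that d = (1−p)f. This uses the pooled SE for the critical value and the unpooled SE for the spread.

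| p | f = 5% | f = 10% | f = 20% |
|---|---|---|---|
| 0.30 | d = 3.5 points, 8% | 7 points, 16% | 14 points, 46% |
| 0.50 | 2.5 points, 6% | 5 points, 10% | 10 points, 25% |
| 0.70 | 1.5 points, 5.5% | 3 points, 7% | 6 points, 14% |

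The effect runs from negligible to large, depending on quantities the documents do not supply.

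**The case against.** The strongest reply is that the protocol nowhere puts knowledge on the CRF. The form contents are not shown, and the enumerator's questionnaire is also in the tool list. The registration table even allows knowledge to be measured at any time after the intervention and places intention at 14 weeks, which the questionnaire could serve. This stands as a limit on certainty. It does not remove the point, because Outcomes (12) puts both measures soon after the intervention and no independent assessor is named for that time.

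Second, filling in a form is not grading. Electronic forms with skip logic, Likert items and a Cronbach's alpha criterion fit recorded client answers at least as well as provider judgement. This also stands: interviewer influence is possible, but discretionary upgrading is not shown.

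Third, booking is a concrete act that leaves a dated card, and whoever books will naturally record it. That is fair. The main fault of the card measure is that appointments belong to the intervention, and changing the recorder alone would not cure this.

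Fourth, the size of the shift is assumed, and uptake, the main outcome in Outcomes (12), is collected by an enumerator. Both are correct and limit the weight of the point.

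A reader might infer more: that counsellors score their own clients and inflate results in both intervention arms and only there. The documents do not support this. Overlap is clear only in the facility arm, control CRFs are presumably provider-filled too, and nothing is said about what stake control staff have.

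**Conclusion.** The point holds in a limited form. As written, the immediate outcomes rest on tools filled by unblinded care staff, who in the facility arm belong to the group that delivers the intervention, and no independent assessor is named. Recording can therefore favour the intervention. Separately, and on firmer text, a card-based intention measure is not comparable with controls on routine care.

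The conclusion depends on reading the CRF as the source of knowledge. The 10-11% and 25-30% false-positive rates depend on assumed shifts of 5 and 10 points, 82 per arm, independence and true proportions of 27% to 50%; they are not estimates for this trial. The 14-week uptake outcome is outside the point. It is worth acting on because the change is cheap and because two sections call these outcomes primary.

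**What to change.** In Recruitment (15), Data collection methods (18a,b) and Data management (19), state that the trained enumerator collects knowledge, stated intention to use postpartum family planning, attitude and perceived control, with the same items in every arm. Use the exit interview already planned; for controls, hold it after the routine antenatal contact. Keep the provider-filled CRF for recruitment data. Report appointment acceptance from the card as a service or process measure, not as the between-arm comparison of intention.

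The cost is a slightly longer exit interview, the same short interview for the 82 controls, and a small rewording of the intention outcome in the registration table, Outcomes (12) and Statistical methods (20a,b,c), notified by the route in Protocol amendments (25). The enumerators will work at sites whose allocation is known and will not be blinded either, so the bias is reduced, not removed.
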